## Abstract

**Background:**

The novel coronavirus has a high mortality rate (over 1% for patients older than 50 years). This can only be partially ascribed to other comorbidities. A possible explanation is a factor that assures a prompt response to SARS-CoV-2 in younger people, independent from the novelty of the virus itself. A factor is believed to stimulate the immune system and provide immunity against more antigens. The only external stimulation received by healthy people is vaccination (eg, the diphtheria, tetanus, and pertussis [DTP] vaccine). One hypothesis is that vaccination helps develop specific immunity but generates sprouting immunity against antigens in transit. The underlying immunological phenomena are the “bystander effect” and “trained immunity.” The developed immunity gives protection for years until it naturally fades out. After the fifth decade of life, the immune system is almost incompetent when a viral infection occurs, and thus, at this stage, the novel coronavirus can enter the body and cause acute respiratory distress syndrome.

**Objective:**

The initial aim is to demonstrate that blood monocytes and natural killer cells show overpowering hyperactivity, while CD4+ and CD8+ T cells experience impediments to their defensive functions in patients with severe SARS-CoV-2 infection. The secondary objectives are to correlate clinical data and vaccination history with laboratory immune patterns in order to identify protective factors. Subsequently, we are also interested in characterizing the phenotypes and state of the degree of activation of peripheral blood mononuclear cells, including monocytes, natural killer cells, and CD4+ and CD8+ T cells, in healthy subjects vaccinated with the Pfizer vaccine.

**Methods:**

Data will be collected using the following 3 approaches: (1) an experimental analysis to study the innate immune response and to identify genetic profiles; (2) an epidemiological analysis to identify the patients’ vaccination history; and (3) a clinical analysis to detect the immunological profile.

**Results:**

The protocol was approved by the Ethics Committee on April 16, 2020, and the study started on April 27, 2020. As of February 2021, enrollment has been completed. Immunological analysis is ongoing, and we expect to complete this analysis by December 2022.

**Conclusions:**

We will recognize different populations of patients, each one with a specific immunological pattern in terms of cytokines, soluble factor serum levels, and immune cell activity. Anamnestic data, such as preceding vaccinations and comorbidities, biochemical findings like lymphocyte immunophenotyping, and pre-existing persistent cytomegalovirus infection, allow depicting the risk profile of severe COVID-19. Proof of the roles of these immunological phenomena in the development of COVID-19 can be the basis for the implementation of therapeutic immunomodulatory treatments.

**Trial Registration:**

ClinicalTrials.gov NCT04375176; https://clinicaltrials.gov/ct2/show/NCT04375176

**International Registered Report Identifier (IRRID):**

DERR1-10.2196/29892

## Introduction

### Background and Rationale

Coronaviruses are common human and animal pathogens. During epidemics, they cause up to one-third of community-acquired upper respiratory tract infections in adults and probably play a role in severe respiratory infections in both children and adults. However, coronaviruses are responsible for a limited amount of diagnosed pneumonia and acute severe illness, especially in the younger population, and a coinfection is frequently detected in hospitalized patients. Usually, the infection is responsible for mild-to-moderate symptoms that rapidly and spontaneously resolve [1].

The new strain of coronavirus, SARS-CoV-2, belongs to the beta-coronavirus family, and it shares all community-acquired coronavirus transmission routes and symptoms. However, the transmission rate is significantly higher, with a faster viral spread responsible for the worldwide outbreak.

In fact, it is a novel virus that was most likely recently passed from bats to humans, and consequently, it is almost unknown to the human immune system. Besides, SARS-CoV-2 seems to undergo modification rapidly during its spread, further avoiding immune defenses [2].

A higher mortality rate characterizes the novel coronavirus, and it has reached over 3% [3]. The death rate is over 1% only for patients aged over 50 years, and it is under 0.4% until 40 years of age. No fatalities have been declared among children under 10 years of age. Furthermore, the death rate is almost double for males when compared with females [4].

The mortality rate distribution of infected patients can be only partially explained by other comorbidities, in addition to older age. Patients with no pre-existing conditions have a fatality rate of 0.9% [4], due to the rapid spread of the virus among the population and within the infected patient, leading to quick and extensive lung injury. However, the near absence of severe illness in children and generally in patients younger than 40 years cannot be explained. Children represent the age group most exposed to all community-circulating viruses, including coronaviruses. Among younger patients, the behavior of the novel virus is similar to that of seasonal community-acquired coronaviruses that can cause severe (but rarely lethal) infections such as pneumonia and bronchiolitis. Indeed, an efficient immune response rapidly counteracts viral infection, even as this virus grows rapidly and changes continuously. In other words, infants, children, and young people could be infected by coronaviruses and by SARS-CoV-2 itself, but the infection is rapidly self-limited, and probably, most of them do not display symptoms. In contrast, older patients experience severe lung injury as a consequence of a slow immune response owing to the novelty of SARS-CoV-2. A possible explanation for these phenomena is a prompt response to SARS-CoV-2 in younger people compared with older people, independent of the novelty of the virus itself. The response might not be specific, but it can limit the infection in the infected host. This is similar to Bacillus Calmette-Guérin (BCG) vaccine immunization in mice that induced nonspecific protective effects against other pathogens such as *Staphylococcus aureus*, *Listeria monocytogenes*, *Salmonella typhimurium*, and *Schistosoma mansoni*. Monocytes and natural killer (NK) cells were believed to play key roles in triggering such trained immunity in murine studies [5]. In addition, the enhancement of monocyte and NK cell responses following BCG vaccination has been reported in humans, and this is due to epigenetic modiﬁcation at the H3K4me3 (trimethylation of lysine 4 on histone H3) level [6].

However, several mechanisms of trained immunity remain unclear, because the trained immune memory–like phenomenon appears to be for a few months or at least a few years. This immunity is not persistent but progressively fades out. Decreased immune response in the elderly could be responsible for more severe acute respiratory disease from coronaviruses in general and higher mortality from COVID-19, since SARS-CoV-2 can cause an explosive attack against the respiratory system, which is similar to major trauma and allows the development of acute respiratory distress syndrome (ARDS). No evident differences were found in different age groups among healthy people, which could justify the drop in immunity against coronaviruses, except its natural fadeout. The trained immune response acts from the age of 2 years, when hypothetical stimulation occurs, to the fifth decade because of its slow decrease.

Vaccines provide external stimulations in healthy people that trigger immune system responses (eg, diphtheria, tetanus, and pertussis [DTP] vaccines stimulate the immune system). Specific vaccines trigger specific immune actions against specific infectious agents, but provide sprouting immunity against antigens in transit, such as those of coronaviruses and other community-circulating viruses [6]. The underlying immunological phenomena are “bystander effect” and “trained immunity.”

Children receive vaccines during the first year of life. Consequently, they become protected against not only specific pathogens but also multiple antigens from pathogens in transit. The developed immunity gives protection against multiple viral infections for years until naturally fading out. After the fifth decade, this immunity is slower to be recalled and reactivated. At this point, a viral infection will find the immune system almost incompetent, and the virus can enter the organism and cause extensive damage. Among elderly people, severe pneumonia and ARDS are frequently noted when they have a coronavirus infection, flu, etc. The history of pandemic viruses reveals an unexplained phenomenon, which could support this hypothesis. In fact, the “Spanish flu” showed a higher mortality rate among young people, especially those aged 20 to 45 years, which could be partly explained by their life conditions after the end of the First World War.

This epidemiological distribution of mortality rate remains unique, and it has not been noted in the successive pandemics of the 21st century [7]. A possible explanation for this is the advent of vaccines, with extensive vaccination after the 1930s. The population received vaccines 20 years before, and the Asiatic and Hong Kong pandemics showed the highest mortality rates after the fifth decade of life when the partially specific immunity had faded [7,8].

Additionally, transplant recipients and HIV-infected patients, characterized by a compromised immune system, unexpectedly do not seem to experience the worst complications of SARS-CoV-2 infection. An immune system imbalance could play a pivotal role during the viral infection, limiting destructive consequences of excessive inflammation.

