#### Secondary Objectives

The secondary objectives are to identify protective factors, using anamnestic data, such as preceding vaccinations, comorbidities, clinical presentation of COVID-19 in terms of clinical signs and symptoms, and biochemical findings. The recognition of a population of patients safe from excessive inflammation against SARS-CoV-2 could define a risk score for the severity of COVID-19, which could allow for the best clinical choice tailored to each patient. Moreover, favorable immunological pattern identification could be followed by implementation of prophylactic or therapeutic immunomodulatory treatments.

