#### Secondary Endpoints

The secondary endpoints are to correlate clinical data and vaccination history with laboratory immune patterns to identify protective factors for severe COVID-19 and break new ground for advanced therapeutic strategies.

Identifying differences between patients having mild infection with positive outcomes and patients having ARDS requiring ventilatory assistance could be useful to optimize the therapy and to come up with an immunostimulant therapy that can produce specific immunity and can decrease the hyperactivity of the innate response and thus the inflammatory condition.

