### Data Collection and Management

Data will be collected using the following 3 approaches: (1) an experimental analysis for clusters of patients to study the innate immune response and to identify genetic profiles; (2) an epidemiological analysis to identify patient vaccination history; and (3) a clinical analysis to detect the immunological profile.

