## Discussion

According to the medical hypothesis on which the protocol is based, young people could benefit from functional adaptation of innate immune cells induced through epigenetic reprogramming and, especially, pre-existing “partially specific” immunity to community viruses associated with the “bystander effect” of preceding vaccinations [6]. In this study, we will explore the main differences among patients infected by SARS-CoV-2 who experience the illness at different degrees of severity. We will recognize different populations of patients, each one with a specific immunological pattern. There could be differences in terms of cytokines, soluble factor serum levels, and immune cell activity (both of the innate compartment and the acquired one). In this way, the contribution of trained immunity and the bystander effect to protection against SARS-CoV-2 could be explained. Anamnestic data, such as preceding vaccinations and comorbidities, biochemical findings like lymphocyte immunophenotyping, and pre-existing persistent cytomegalovirus infection, allow depicting the risk profile of severe COVID-19. Proof of the roles of these immunological phenomena in the pathogenesis of COVID-19 can be the basis for the implementation of therapeutic immunomodulatory treatments. In addition, the definition of an immunological risk profile could tailor established therapies to each type of patient.

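### Time since childhood vaccination nearly equals age, and the stated methods carry no age term, so a crude vaccination-history association cannot be told from ageing

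*Protocol article*

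**What the plan says.** Background and Rationale places the stimulus early in life: "Children receive vaccines during the first year of life". It continues: "The developed immunity gives protection against multiple viral infections for years until naturally fading out". The same section dates the effect slightly differently: "The trained immune response acts from the age of 2 years, when hypothetical stimulation occurs, to the fifth decade because of its slow decrease". On either account the dose comes in infancy or soon after, and protection declines over decades.

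The exposure to be analysed is described more broadly. Secondary Objectives aims "to identify protective factors, using anamnestic data, such as preceding vaccinations, comorbidities". Secondary Endpoints states: "The secondary endpoints are to correlate clinical data and vaccination history with laboratory immune patterns to identify protective factors for severe COVID-19". Data Collection and Management lists "an epidemiological analysis to identify patient vaccination history", and the closing paragraphs of the section on plasma and PBMC preparation name regional health archives as the source for missing data. None of these sections says which vaccines, which doses or which dates define the exposure.

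Statistical Methods names Pearson correlation, the Wilcoxon matched pairs test, the Mann-Whitney test and one-way ANOVA. None of them, as listed, includes a covariate. The Discussion then expects that "the contribution of trained immunity and the bystander effect to protection against SARS-CoV-2 could be explained".

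**The concern.** The hypothesis offers faded vaccine training as the reason why older people fare worse. Age is the obvious rival explanation, and the Introduction itself reports death rates above 1% only over age 50 and below 0.4% up to age 40. Patients and controls need only be at least 18, and no age matching is described, so age can be expected to differ between severity groups.

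If the exposure is how long ago a childhood dose was given, it is almost the same variable as age. A correlation of that exposure with severity or with an immune marker would look the same whether vaccine training had faded or patients were simply older. At stake is the secondary question, whether earlier vaccination protects against severe COVID-19, and the Discussion's claim about trained immunity. The primary immunophenotyping objective is not affected.

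**Working it through.** The plan gives no figure for this point. Its 30 patients per group and its detectable difference of 20% to 30% (Sample Size) do not bear on it. The document gives no age distribution, vaccination uptake or dose dates, so those inputs are assumptions.

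**1. Collinearity for childhood doses.** Let T = age − U, where U is age at the dose.
- Assumed: U uniform on 0 to 2 years, so Var(U) = 2²/12 = 1/3, independent of age; age SD 15 years, varied from 12 to 18.
- R² of T on age = SD²/(SD² + 1/3) = 225/225.333 = 0.9985.
- VIF = 1/(1 − R²) = 1 + 3·SD² = 1 + 3·225 = 676.
- Standard error multiplier = √676 = 26.

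| Age SD (assumed) | VIF | SE multiplier |
|---|---|---|
| 12 | 433 | 20.8 |
| 15 | 676 | 26.0 |
| 18 | 973 | 31.2 |

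A simulated check with 120 patients and age uniform from 18 to 90 gave a VIF of about 1,260 for doses at 0 to 2 years and about 5,200 for doses within the first year. If everyone is dosed at the same age, the design matrix of intercept, age and time since dose has rank 2 of 3, and the two effects cannot be separated at all.

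**2. What stays estimable.** Suppose doses are given only in infancy but some patients are unvaccinated. The median VIF of ever-vaccinated given age was then:
- 1.0 if uptake (50% or 80%) is unrelated to age;
- 1.6 if uptake falls gradually with age (50% at age 60);
- 3.7 if uptake stops sharply at a cohort cutoff of age 60.

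In each case the model with age, vaccination and their interaction had full rank (4 of 4).

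**3. Power of that route at n = 120.** Simulated outcome: a decline of 0.02 SD per year of age, plus a vaccine effect of 1 or 2 SD at birth that fades linearly to zero at age 50, with 50% or 80% vaccinated independently of age. The test was the linear vaccination-by-age interaction at two-sided 0.05.
- No vaccine effect: rejection 4.7% to 5.2%, so the test keeps its size.
- 1 SD effect: power 11% to 15%.
- 2 SD effect: power 29% to 44%.

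**4. Adding dated adult doses.** If some patients also have an adult dose at a random date, the VIF of time since last dose given age falls from about 5,250 (none) to 4.0, 2.0 and 1.6 when 10%, 30% and 50% have one (assumed shares).

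**The case against.** A reader might infer that the plan's exposure is infant vaccination, that no analysis of these data could separate fading from ageing, and that only adult doses would do. The documents do not support that reading.

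- The sentence about first-year vaccines is background. The sections that state what is analysed speak of preceding vaccinations and vaccination history without an age limit. The Introduction also describes trained immunity as lasting months or years, which fits recent doses.
- Collinearity binds one variable, time since a childhood dose, among people who all had it. Whether, which and how many vaccines were received can differ at the same age, and step 2 shows that such contrasts are estimable. Low power is not non-identifiability.
- Near-universal childhood uptake would have to be assumed. The document gives no uptake data, and its remark that vaccination became widespread only after the 1930s points to differences between birth cohorts.
- The VIF of 676 belongs to a model that the plan does not specify.

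All of this stands, and it limits the point. It does not remove it. Variation between birth cohorts is itself tied to age. The methods that the article does list are unadjusted, and its Discussion draws the mechanistic conclusion. It can also be said that a condensed article leaves variable coding to a fuller document. That is fair for the coding. But simply adding age later, the usual remedy, would not rescue a time-since-childhood-dose variable, so the limit on interpretation belongs with the hypothesis.

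**Conclusion.** The point holds in a bounded form. For childhood doses, the fade-out hypothesis is nearly collinear with age: the VIF is 433 to 973 for an assumed age SD of 12 to 18 years and a dose at age 0 to 2. With the methods listed, an association between vaccination history and severity or immune pattern cannot be told from an age effect. Age adjustment leaves time since a childhood dose practically without information, but it does allow contrasts of whether, which or how many vaccines were received. Under the simulated scenarios those contrasts are weak for detecting fading: at most 15% power for a 1 SD effect and 44% for 2 SD. The age distribution, uptake and adult-dose shares are all assumed. The qualitative conclusion on collinearity does not depend on their exact values, but the power figures do. A change should be made because a secondary objective and its interpretation are affected.

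**What to change.** 1. In Secondary Endpoints and Statistical Methods, analyse vaccination history by regression, with severity group or immune marker as outcome and age and recorded comorbidities as covariates. Keep the crude correlations as description only.
2. Define exposures that can vary at a given age: each vaccine received or not, number of doses and, where the history or the archive gives dates, recent adult doses and time since the last dose. These come in addition to childhood vaccination and do not replace it.
3. In the Discussion, state that fade-out of childhood vaccination cannot be reliably separated from ageing in this study.

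The age term and the added statement cost almost nothing. Coding dose dates takes work and depends on their being available. The document does not show that they are, and it reports the clinical data set as complete, so this should be checked first. Adjusted intervals will be wider, and confounding by birth cohort and comorbidity will remain in part.

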### Pathophysiological Considerations

The immune system monitors tissue homeostasis, eliminates damaged cells, prevents tumor cell development, and protects against pathogens or infectious agents. The first-line defense involves chemical-physical barriers, followed by the action of innate immune cells, such as cytolytic NK cells and phagocytic myeloid cells, including monocytes/macrophages, dendritic cells, and granulocytes. These cells are activated by the recognition of specific molecular profiles shared by different families of pathogens (Toll-like receptor [TLR], nucleotide oligomerization domain–like receptor, and caspase activation and recruitment domain), including bacteria and viruses, and the innate immune system acts quickly (within minutes/hours). On the other hand, the acquired immune system requires from 4 to 8 days to develop a primary response, and it is able to eliminate infectious agents more effectively due to the extremely specific recognition function of lymphocytes.

In addition, a characteristic of the acquired immune response is its ability to generate “immunological memory,” the mechanism through which an organism develops a faster and more effective response against a subsequent exposure to the same infectious agent. The main actors and effector cells of acquired immunity are CD4^+^ T helper (Th) and CD8^+^ T cytotoxic lymphocytes, which are responsible for cellular immunity, and B lymphocytes, which are responsible for humoral immunity. For an effective response in the body, the innate and acquired immune systems cooperate, despite differences in specificity and activation times. However, more recently, it has been highlighted that cells of the innate immune system have a certain type of immunological memory [9-11].

Macrophages are innate immune cells that belong to the phagocyte cell type. They reside in all tissues and are the mature forms of monocytes, which circulate in the blood and continuously migrate to tissues where they differentiate. They live relatively long and perform several functions in the innate immune response and subsequent acquired immune response [9]. They have a defensive role against pathogens, and have roles in tissue homeostasis and the inflammatory process. Macrophages can be classified as classically activated M1 and alternatively activated M2 macrophages based on their distinct functional capacities in response to stimuli from the microenvironment. M1 macrophages are stimulated by bacterial infections and cytokines produced by Th1 lymphocytes (interferon [IFN]γ), and have roles in the defense against pathogens and killing of cancer cells. M2 macrophages are stimulated by cytokines produced by Th2 lymphocytes (interleukin [IL]-4 and IL-13), and promote physiological and tumor angiogenesis, wound repair, and suppression of immune responses [12-14]. The induction of specific macrophage functions is closely related to the surrounding microenvironment, which acts as an internal regulator. This phenomenon, called polarization, derives from cell-cell/cell-molecule interaction, which governs the functionality of macrophages within host tissues.

Moreover, enhanced responses of a type similar to memory responses (bystander effect or trained immunity) have been highlighted by various studies on monocytes and macrophages [9]. The mechanism involves epigenetic modification of these phagocytes, with enhanced responses in terms of increased responses through TLRs and the release of proinflammatory cytokines, particularly following BCG vaccination for up to 1 year postvaccination [15]. There is also epidemiological evidence indicating that other vaccines, such as the smallpox vaccine and DTP vaccine, could have beneficial contrasting effects on other microorganisms [16].

Interestingly, the release of delayed IFNα from inflammatory monocytes/macrophages has been shown to play a key role in a mouse model of SARS-CoV-2 infection with pulmonary hyperinflammation [17]. Only genetic depletion of the IFNα/β receptor protected mice from death. In addition, other cytokines released by inflammatory monocytes, such as IL1β, IL-6 (also confirmed in COVID-19 patients recently [18]), and inducible nitric oxide synthase, appeared important.

Therefore, the M2 phenotype (the type representing repairing or constructing macrophages) appears to be the one required to inhibit a strong M1 proinflammatory response associated with the late severe phase of ARDS. Multiple interactions between monocytes/macrophages and NK cells have been described both in vitro in humans [19] and in vivo in a mouse model [20]. In the case of a melanoma metastasis mouse model, Sommariva et al showed that vaccine stimulation with TLR3 that recognizes viral double-stranded RNA (the agonist that mimics this response is polyinosinic polinosinic polycytidylic acid [poly I:C]) and TLR9 that recognizes bacterial DNA (CpG) was able to trigger bidirectional crosstalk between lung alveolar M1-type macrophages and NK cells [20].

NK cells are innate cells and represent 10% to 20% of circulating lymphocytes, a proportion that can vary with age. They are phenotypically characterized by the expression of the CD56 membrane molecule and the lack of expression of the CD3 molecule. They are a population of cells with cytotoxic activity toward cancer cells or virus-infected cells, in which they induce apoptosis owing to the release of perforins and granzymes contained within them. More recently, however, some trained immunity functions of these cells have been characterized, with memory-like responses [21,22] and regulatory functions toward monocytes [23]. The NK subtype with the CD56^dim^CD16^+^ phenotype, which represents about 90% to 95% of NK cells in peripheral blood, has perforin and granzyme release activity with cytotoxic action. The other subtype with the CD56^bright^CD16^−^ phenotype, which represents 5% to 20% of NK cells in peripheral blood, does not have cytotoxic action, but secretes high levels of cytokines such as IFNγ and tumor necrosis factor (TNF)α. However, it has been shown that this second subgroup when exposed in vitro to IL-2, IL-12, or IL-15 can assume a CD56^dim^CD16^+^ phenotype and therefore have cytotoxic activity. A third subpopulation has been identified in pregnancy at the deciduous level, where mechanisms of tolerance toward the fetus must be activated. During the first trimester of pregnancy, decidual NK (dNK) cells with the CD56^superbright^CD16^−^ phenotype show a high incidence up to 50% among immune cells. dNK cells are poorly cytolytic and exhibit proangiogenic functions by releasing vascular endothelial growth factor, placenta growth factor, and IL-8. In the tumor field, it has been shown that NK cells similar to dNK expand at the tumor site and are involved in the mechanism of tumor angiogenesis associated with the growth of solid tumors [24-28]. Furthermore, recent studies have suggested that peripheral blood CD56^bright^CD16^−^ NK cells may play a role in regulating the immune response as they produce adenosine, an immunosuppressive molecule, and are capable of inhibiting the proliferation of CD4^+^ T cells, with a possible regulatory role in autoimmune diseases [29].

There will be an extension of the “Coronavirus Project” aim to study the cells involved in the immune response in order to understand the consequences of specific vaccine stimulation against SARS-CoV-2, parallel to the standard humoral response.

Approximately 60 subjects (aged ≥18 years) from the health care workforce, for whom the date of the first administration of the Pfizer vaccine is already defined, will be studied at the following 3 time points: T0, prior to or on the day of the first administration of the vaccine; T1, between the 14th day after the first administration and the day of the second administration; and T2, between the 32nd and 35th days after the first administration.

